## Abstract

Purpose: The primary aim will be to assess the effects of prone positioning (tummy time) on cervical extension (angular kinematics and time) in preterm infants. The secondary aim will be to assess the effects of tummy time on gross motor function. Methods: This randomized, controlled clinical trial will include 40 preterm infants weighing less than 2500 g, randomly allocated into control or experimental group (n = 20) and followed up from birth to six months of corrected age by the team of the neonatal follow-up clinic. Caregivers will be routinely guided on bonding, developmental milestones, and how to perform the tummy time for 30 min throughout the day (experimental group). An illustrative booklet will be provided as support material. The hypothesis will be tested using inferential analysis, considering an alpha of 5%. Discussion: We expect tummy time to strengthen cervical muscles needed to overcome gravity, master motor skills, and stimulate the integration between family activity and environmental experiences, considerable challenges to which preterm infants are exposed. Trial registration: Registered in the Brazilian Registry of Clinical Trials (identifier RBR-2nwkr47) on 17 February 2022.

## 1. Introduction

The American Academy of Pediatrics [1], using the Back to Sleep educational campaign [2], recommended avoiding prone positioning when sleeping to reduce the number of sudden deaths in newborns in the United States. This practice spread worldwide and reduced the number of unexpected mortalities. However, the prolonged use of the supine position delayed neuromotor development [3,4] and increased the cases of cranial asymmetry (e.g., positional plagiocephaly and brachycephaly) [5]. Therefore, caregivers began to be encouraged in the use of prone position when infants were awake to reduce morbidities associated with the supine position and increase play and family bonding [6,7]. This practice, also known as tummy time [8], was then disseminated worldwide through the educational campaign Back to Sleep, Tummy to Play [9].

Tummy time is also encouraged by the World Health Organization (WHO) [10] for infants under one year of age, possibly becoming the first opportunity for physical activity. Although Brazil does not have a specific recommendation on tummy time, the Brazilian Society of Pediatrics follows the recommendations of the American Academy of Pediatrics [11] and the WHO [10]. Tummy time can be performed starting at birth, strengthening the head, neck, and trunk muscles needed to overcome gravity and master motor skills (e.g., rolling over, sitting, crawling, and switching positions) [4,12]. Two systematic reviews found an association between tummy time and the prevention of positional skull deformity [3,13], which delays motor development. Studies also indicated that this delay might be due to limited head movement [14] or cranial alteration in brain formation [15].

Studies established a relationship between tummy time and motor development in infants with typical and atypical development [12,16]. These effects may also extend to preterm infants at risk of developmental delays due to immaturity of the neurological [17] and musculoskeletal systems [18].

Premature birth hinders essential and organizing experiences needed for good intrauterine development, possibly leading to changes in brain maturation and negatively impacting the interaction between caregiver and infant. Moreover, family engagement and empowerment are essential to improve the environment and development of a preterm infant [19].

Tummy time can notably integrate family activity and environmental experiences, considerable challenges to which preterm infants are exposed [20,21]. Mendres-Smith et al. [7] observed that tummy time conducted by parents decreased negative vocalizations and increased exercise tolerance in infants. Thus, this study hypothesizes that tummy time will provide adequate motor development in preterm infants, especially for motor skills in the first months of life. The primary aim will be to assess the angular kinematics of the cervical extension; the assessment of gross motor function will be the secondary aim.

## 2. Materials and Methods

### 2.1. Study Setting and Participants

This randomized, controlled, and double-blinded clinical trial will be reported according to the Consolidated Standards of Reporting Trials (CONSORT) [22] and the Template for Intervention Description and Replication checklist (TIDieR) [23].

Data will be collected at the Pediatrics and Childcare outpatient clinic of the Januario Cicco Maternity School of the Federal University of Rio Grande do Norte (Natal, Rio Grande do Norte, Brazil). The sample will comprise preterm infants born in the maternity school, followed up at the clinic, and recruited via direct contact with the caregivers by the researchers.

### 2.2. Sample Size

The sample size was calculated using the G Power software, considering the Ancova test. The randomized controlled pilot study of Flierman et al. [24] was considered to determine the effect size (Cohen’s d). The estimated minimum sample size was 40 preterm infants, considering the gross motor subtest of 9.1 ± 1.7 and 8.1 ± 2.0 (Cohen’s d of 0.59), two groups, four assessments, sampling error of 0.05, and a power of 0.80.

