#### 2.8.5. Data Analysis

Data analysis will be performed by a researcher blinded to allocation, using the Statistical Package for the Social Sciences software (IBM, Armonk, NY, USA). Only the primary investigator (not involved in data collection) may stop the study and have access to the final data.

The descriptive analysis will be presented as measures of central tendency and dispersion, and the inferential analysis will consider a statistical significance of 5%. The Shapiro–Wilk test will analyze data distribution. Moreover, the split-plot ANOVA will be used to compare differences between groups and assessments, and linear mixed models will analyze possible differences between groups. Regarding the interventions, the *t*-test for independent samples or the Mann–Whitney test will be used for intergroup comparisons.

Group description will be presented as mean and SD, and the effect size and 95% confidence interval will be reported. The intent-to-treat analysis will be performed for missing data, considering the last data of the preterm infant.

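### Section 2.2's means and SDs give Cohen's d = 0.54, not 0.59, and the stated power of 0.80 with 40 infants is not supported for the planned split-plot ANOVA

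*Protocol article*

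**What the plan says.** Section 2.2 names the method: "The sample size was calculated using the G Power software, considering the Ancova test". The inputs come from a cited randomised pilot: "The estimated minimum sample size was 40 preterm infants, considering the gross motor subtest of 9.1 ± 1.7 and 8.1 ± 2.0". The rest of the sentence gives the effect size and settings: "Cohen’s d of 0.59), two groups, four assessments, sampling error of 0.05, and a power of 0.80".

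Section 2.8.4 defines the four assessments as one baseline at hospital discharge and three later ones at 2, 3 and 4 months of corrected age. The Abstract puts 20 infants in each group. For the analysis, Section 2.8.5 says that "the split-plot ANOVA will be used to compare differences between groups and assessments"; the same sentence adds linear mixed models for group differences, without saying whether baseline enters as a covariate. Sections 2.7.1 and 2.7.2 make cervical-extension kinematics and time the primary outcome and Bayley-III gross motor function the secondary one.

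**The concern.** The sample size rests on one effect size, and that figure disagrees with the means and SDs printed beside it. The error favours the trial: a larger d gives more apparent power for the same 40 infants.

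The second problem is the link between sizing and analysis. The sizing is labelled ANCOVA, while the first analysis named is a split-plot ANOVA that counts the pre-intervention visit as one of its four levels. Randomised groups should not differ on average at that visit, so including it dilutes the group effect. If the protocol's 0.80 does not apply to the test that is reported, a non-significant result could be read as evidence of no effect from a trial thought to have had an 80% chance of finding one.

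**Working it through.** **Inputs.** From 2.2: means 9.1 and 8.1, SDs 1.7 and 2.0, alpha 0.05, power 0.80, N = 40, two groups, four assessments. From 2.8.4: one baseline and three follow-ups. Assumed, because not stated: two-sided test, equal correlation r between any two visits, no group difference at baseline, and the same difference d at each later visit. I used r = 0.3, 0.5 and 0.7.

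**Effect size.**
- Pooled SD = √((1.7² + 2.0²)/2) = √3.445 = 1.856.
- d = 1.0/1.856 = 0.539, so f = d/2 = 0.27.
- Smaller SD only: 1.0/1.7 = 0.588, the printed 0.59. Larger SD only: 1.0/2.0 = 0.50.
- Unequal pilot arms do not explain it: with 90% of the weight on SD 1.7, d is 0.577.
- Rounding could: if each printed figure is off by up to half a unit in its last place, the pooled d lies between 0.9/1.906 = 0.47 and 1.1/1.806 = 0.61.

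**Reproducing the plan's figure.** Take the mean of three follow-ups adjusted for baseline. In SD units its variance factor is v = (1 + 2r)/3 − r², with noncentrality λ = N(d/2)²/v on 1 and 37 df. With d = 0.59 and r = 0.5, v = 0.667 − 0.25 = 0.4167 and λ = 40 × 0.295²/0.4167 = 8.35, giving power 0.80. So 40 infants can be reached this way, at an assumed r = 0.5 and the uncorrected d.

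**Split-plot group effect.** The expected difference in four-visit means is 0.75d, and the variance of a four-visit mean is (1 + 3r)/4. Hence λ = N(0.75d)²/(1 + 3r) on 1 and 38 df. At d = 0.59 and r = 0.5: 40 × 0.1958/2.5 = 3.13, power 0.41.

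**Split-plot interaction.** The differences 0, d, d, d have a sum of squares about their mean of 0.75d². Hence λ = (N/4) × 0.75d²/(1 − r) on 3 and 114 df. At d = 0.59 and r = 0.5: 10 × 0.261/0.5 = 5.22, power 0.44.

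**Power with 40 infants.**

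| Test | d | r = 0.3 | r = 0.5 | r = 0.7 |
|---|---|---|---|---|
| Split-plot, group | 0.59 | 0.51 | 0.41 | 0.34 |
| Split-plot, group | 0.54 | 0.44 | 0.35 | 0.29 |
| Split-plot, interaction | 0.59 | 0.33 | 0.44 | 0.68 |
| Split-plot, interaction | 0.54 | 0.28 | 0.38 | 0.59 |
| Baseline-adjusted mean of three | 0.59 | 0.78 | 0.80 | 0.90 |
| Baseline-adjusted mean of three | 0.54 | 0.70 | 0.73 | 0.85 |

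**Outside that range.** The group test stays below 0.80 even at r = 0 (λ = 40 × 0.1958 = 7.83, power 0.78 at d = 0.59). The interaction reaches 0.80 at about r = 0.77 for d = 0.59 (λ = 2.611/0.23 = 11.35) and about r = 0.81 for d = 0.54 (λ = 2.177/0.19 = 11.46). At d = 0.54 the baseline-adjusted mean reaches 0.80 from r of roughly 0.65 (v = 0.344, λ = 8.43, power 0.81), and otherwise only near zero correlation (0.82 at r = 0, 0.76 at r = 0.1).

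**Fewer infants.** If 18 per group were analysed (an assumption), the baseline-adjusted mean at d = 0.54 and r = 0.5 gives 0.68.

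**The case against.** The best defence is that 2.2 names an ANCOVA with four assessments, and that one baseline plus three follow-ups gives 0.80 at d = 0.59 and r = 0.5. The mixed model in 2.8.5 could be set up that way. A condensed article may also leave the correlation and software settings to a fuller document. All of this stands. The missing correlation is not the fault here. The fault is a wrong d, and a power figure that does not carry over to the split-plot test.

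Two other routes to 0.80 fit this trial poorly. A repeated-measures between-groups calculation gives 0.82 at r = 0.2, but it assumes the full difference at all four visits, baseline included; with none at baseline it gives 0.58 (λ = 40 × 0.1958/1.6 = 4.90). A standard interaction calculation gives at least 0.88 at d = 0.59, but it takes d/2 directly as the size of the interaction, which the pattern 0, d, d, d does not produce.

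The defence can also say that rounding might explain 0.59 and that the cited pilot is not visible. That stands as a possibility; the printed figures still give 0.54.

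A reader might infer more than the document supports:
- That 40 infants cannot give 0.80 and more than 90 are needed. A total of about 94 follows only for one visit with a covariate that explains nothing, which discards the baseline and repeated visits that 2.2 says were counted.
- That d was typed into the field for f. Some settings would then return 40, but so does the baseline-adjusted calculation above, and the settings are not given.
- That the analysed number is bound to fall below 40. Section 2.4 allows exclusions after randomisation, but 2.8.5 promises intention-to-treat with the last value carried forward. It may fall; the document does not settle it.

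**Conclusion.** The concern holds in two parts. First, by the printed inputs d is 0.54, not 0.59. This is plain arithmetic, subject only to the unverifiable possibility of rounding in the source. Second, the stated 0.80 is not supported for the split-plot ANOVA: at correlations of 0.3 to 0.7, power is 0.33 to 0.68 at the stated d and 0.28 to 0.59 at the corrected one, taking both tests together. These figures rest on compound symmetry, no baseline difference, a constant later effect and two-sided 5%.

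The document does not show that 40 infants cannot give 0.80 under any analysis. A baseline-adjusted mean of the follow-ups is close, at 0.73 for d = 0.54 and r = 0.5, and passes 0.80 at a correlation of roughly 0.65 to 0.7 or above. All of these powers refer to gross motor function. None describes the power for cervical extension, the primary outcome.

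**What to change.** In Section 2.2:
- Replace d = 0.59 by d = 0.54 (f = 0.27), or show the unrounded pilot figures that yield 0.59.
- State that the calculation concerns gross motor function, the secondary outcome.
- Name the test and the assumed within-infant correlation, and restate the power of 40 infants for that test. An example, with the correlation as an assumption: about 0.73 for the baseline-adjusted mean of three follow-ups at 0.5, range 0.70 to 0.85 for 0.3 to 0.7, possibly lower after the exclusions in 2.4.

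In Section 2.8.5:
- Specify that baseline-adjusted contrast within the mixed model already planned.
- State that a non-significant result will be interpreted by its 95% confidence interval, which the section already promises, and not as evidence of no effect.

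The cost is wording and a less favourable stated power. Enrolment stays at 40.

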### 2.3. Inclusion Criteria

We will include preterm infants born between 30 and 36 weeks and 6 days (confirmed by ultrasound); with adequate gestational age; Apgar ≥ 7 in the 5th minute; birth weight < 2500 g; without cardiorespiratory, neurological, musculoskeletal, and auditory complications; without genetic syndromes, congenital infections, and visual changes; and with a poor or unusual motor repertoire in the assessment of generalized movements.

### 2.4. Exclusion Criteria

We will exclude preterm infants diagnosed with grade III and IV intraventricular hemorrhage and those whose caregivers withdraw. After the randomization, we will exclude preterm infants who present any worsening of health and need hospitalization, those who move from the state, who do not attend two evaluations, and those whose caregivers do not answer the phone for three consecutive days to reschedule the assessments.

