#### 2.8.4. Assessment

A research team will be responsible for assessments and will be blinded to allocation. Four assessments will be performed: one pre-intervention (baseline) and three post-intervention. The baseline assessment will be at hospital discharge (beginning of the intervention), and the next will be performed at 2, 3, and 4 months of corrected age. Figure 2 shows the study schema.

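### Section 2.4 removes infants after randomisation, which on its plain reading contradicts the intent-to-treat analysis promised in 2.8.5 and can bias the group comparison

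*Protocol article*

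**What the plan says.** Section 2.4 (Exclusion Criteria) lists four grounds that apply once an infant has been allocated. The first is a health event: "After the randomization, we will exclude preterm infants who present any worsening of health and need hospitalization". The next two are "those who move from the state, who do not attend two evaluations". The last is "those whose caregivers do not answer the phone for three consecutive days to reschedule the assessments". The same section also excludes "those whose caregivers withdraw", without saying whether this means before or after randomisation.

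Section 2.8.5 (Data Analysis) says: "The intent-to-treat analysis will be performed for missing data, considering the last data of the preterm infant". It also names a split-plot ANOVA and linear mixed models. Section 2.8.4 sets the visits: "Four assessments will be performed: one pre-intervention (baseline) and three post-intervention". Baseline is at hospital discharge and the later visits are at 2, 3 and 4 months of corrected age.

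The article defines no analysis set beyond this. It does not say that infants excluded under 2.4 stay in the analysis, or that exclusion means only that follow-up stops.

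**The concern.** An intent-to-treat analysis keeps every randomised infant in the allocated group. Section 2.4, read plainly, takes some of them out because of events that happen after allocation. What is left is no longer protected by randomisation.

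The grounds for removal may be linked to arm or to prognosis:

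- Only experimental caregivers are given a daily task (2.8.3), and caregivers know which guidance they receive (2.5 asks them not to reveal it). Attendance and phone contact could therefore differ by arm.
- Worsening health that leads to hospital admission could plausibly go with poorer motor development.
- The hospitalisation rule does not depend on missing data. An infant who is admitted but attends every visit would still be removed.

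With 20 infants per group, a handful of removals could matter.

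**Working it through.** **1. The two rules side by side.** Section 2.4 removes an infant after two missed evaluations. Section 2.8.5 fills gaps with the infant's last value. There are three post-baseline visits (2.8.4). For an infant who stops attending:

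| Last visit attended | Later visits missed | Under 2.4 |
|---|---|---|
| Baseline | 3 | removed |
| 2 months | 2 | removed |
| 3 months | 1 | kept, one value carried forward |

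So for missed visits, carry-forward operates only where a single visit is missed. Early losses, for which an intent-to-treat rule matters most, are outside it.

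**2. The yardstick.** Section 2.2 prints d = 0.59 from gross motor scores of 9.1 ± 1.7 and 8.1 ± 2.0. Dividing the difference by the smaller SD gives (9.1 − 8.1)/1.7 = 0.588, which matches the printed figure. With equal-weight pooling, the SD is √((1.7² + 2.0²)/2) = 1.856 and d = 1.0/1.856 = 0.54. The printed 0.59 is used below. It refers to gross motor function, the secondary outcome, and gives no scale for cervical extension, the primary outcome.

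**3. Harsh illustration (all inputs assumed).** A share p of one arm is removed, those infants average 1 SD below their arm's mean, and none are removed from the other arm. Setting the full-arm mean to 0, 0 = p(−1) + (1 − p)m, so the remaining mean is m = p/(1 − p).

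- p = 10% (2 of 20): 0.10/0.90 = 0.11 SD; 0.111/0.59 = 19% of the printed d.
- p = 20% (4 of 20): 0.20/0.80 = 0.25 SD; 0.25/0.59 = 42% of the printed d.

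**4. Milder illustration (all inputs assumed).** There is no true effect. In each arm the infants with the poorest health are removed, health is normal, and its correlation with the outcome is ρ. The mean health of those who remain is φ(z_p)/(1 − p).

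- 5% removed: 0.1031/0.95 = 0.109
- 20% removed: 0.2800/0.80 = 0.350
- Difference: 0.350 − 0.109 = 0.241, multiplied by ρ
- ρ = 0.3, 0.5, 0.7: bias 0.07, 0.12, 0.17 SD

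With 19 and 16 infants left, the standard error is √(1/19 + 1/16) = 0.339 SD. The nominal 5% two-sided test then has a false-positive rate of about 0.055, 0.065 and 0.079 respectively. Swapping the two rates between arms reverses the sign. With 10% removed in each arm by the same mechanism, the two shifts are equal and the bias is 0.

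**The case against.** The strongest defence is that 2.4 may describe only the end of follow-up, as its wording about moving away and failing to reschedule suggests, with 2.8.5 then carrying the last value forward for those infants. On that reading all randomised infants are analysed. Even on the plain reading, both rules can be applied mechanically; the result is simply not an intent-to-treat set. A reader might infer that the two sections cannot both be followed. That is too strong: the text is contradictory on its plain reading and ambiguous otherwise. The charitable reading is nowhere stated, however, and it has a cost of its own: an infant lost after baseline would carry the hospital-discharge value to 4 months of corrected age.

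A reader might also infer that the comparison is biased, or that the infants doing worst will leave it. The documents do not support this. Bias needs removal that differs by arm, or that relates to outcome differently in the two arms. Moving away and unanswered calls have no documented link to motor outcome, and 2.8.2 provides weekly calls to all caregivers in both groups, which may limit differential disengagement. The possibility remains, because only one group carries the daily task.

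Finally, a reader might infer that hospitalisations, as the main sign of harm, will go uncounted. The article does not give them that status and does not say they will go unreported. It commits to CONSORT reporting (2.1), and safety tables are commonly left to a fuller document.

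**Conclusion.** The conflict between 2.4 and 2.8.5 is real on the plain reading and needs to be resolved before analysis, because two analysts following the article could analyse different infants. Confidence is high on the textual conflict and low on the size or direction of any bias.

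The 0.11-0.25 SD shift is a harsh, one-sided case and the 0.07-0.17 SD range a milder one. Neither is an estimate for this trial: the removal rates, the 1 SD deficit and the correlations are all assumed. Similar removal in both arms would give little or no bias.

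**What to change.** In 2.4, delete the post-randomisation events as grounds for removal from the analysis. In 2.8.5, define the analysis set as all randomised infants in their allocated group, and state that stopping follow-up is separate from removal from the analysis.

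Invite infants who are hospitalised, move or miss visits to the remaining assessments, unless the caregiver withdraws consent for further data.

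Analyse all available assessments with the linear mixed model already named in 2.8.5, in place of carrying the last value forward. The model can use infants with incomplete visits, on the assumption that missingness is explained by the observed data. Report hospitalisations and losses by arm.

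The cost is rewording 2.4 and 2.8.5 and attempting a few visits for infants who would now be dropped. The number randomised does not change.

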### 2.5. Randomization and Blinding

Randomization will be stratified by gender and preterm infants will be separated into two groups using a computer-generated randomization sequence [25]. Three researchers, not involved in the study, will be responsible for allocation and assessments of the infants and for data analysis. The allocation will be sealed in opaque envelopes at the assignment and will keep the randomization confidential during the study. The assessments results will not be disclosed to the researcher responsible for the interventions and the data will be tabulated with a predetermined encoding by another blinded evaluator.

Another researcher not involved in the study and blinded to the allocation will conduct all assessments; results will not be disclosed to the researcher responsible for the interventions. The parents will be instructed, previously, not to tell the researcher what kind of orientation they are receiving. Figure 1 illustrates the protocol according to Standard Protocol Items: Recommendations for Interventional Trials (SPIRIT) [26].

